### Intervention development

The intervention was developed based on the biopsychosocial model of health and illness^27^ with the aim to address biological, psychological and social factors and symptom reduction and relapse prevention. The content was informed through a review of the literature and a series of focus groups conducted with carers. Thematic analysis of focus group data revealed specific difficulties and challenges experienced by carers in the early poststroke aftermath, and helpful coping strategies commonly used. We also conducted a nominal group approach with stroke rehabilitation experts to further refine the intervention. The biopsychosocial intervention was designed to recognise and target the difficulties commonly experienced by informal carers (identified through the focus groups and from the stroke literature). Additionally, helpful coping strategies used by the informal carers were used to further inform and adapt the content of the intervention. More detailed information about the development of the intervention will be provided in a further publication.

### Intervention and comparator

Participants are randomised as dyads. Participants will be randomised to either:
**Control group: usual care.** Carers randomised to the control group will receive the usual range of routine care and services available to them. They will not receive the biopsychosocial intervention.
**Intervention group: biopsychosocial intervention, plus usual care**
Carers randomised to the intervention group will receive the biopsychosocial intervention, in addition to usual care. The stroke carers randomised to receive the intervention will receive a 2-hour session once a week for 6 weeks. The time point at which the intervention will start will be agreed with the carer, in conjunction with other carers likely to be part of that group. This will occur when the stroke survivor they care for has been discharged from hospital, up to 1 year poststroke. We will aim to deliver the intervention to groups of approximately five people. However, in the event that it is not possible to coordinate sufficient people, or where carers are unable to attend the group sessions, we will deliver the intervention on a one-to-one basis or in smaller groups. We will record this as part of our feasibility. The intervention will be delivered at a suitable venue, with sufficient space and access for carer group members. The intervention sessions will be facilitated by a research psychologist who has received training in the principles of biopsychosocial theory as well as specific training from members of the research team responsible for the development of the intervention. Clinical supervision and debriefing sessions will be provided by an experienced community mental health nurse with significant community stroke team experience and/or a clinical psychologist. Each session will last approximately 2 hours and will include a 15 min tea/coffee break that will allow participants to interact more informally with one another, and the session will conclude with a 15 min relaxation exercise. We anticipate that in the definitive trial, the intervention could be delivered by assistant psychologists with supervision from clinical psychologists.The intervention programme is focused on adjustment to stroke, provision of psychoeducation and psychological support. The group programme is based on the principles of the biopsychosocial model. The sessions are designed to teach individuals to identify and use skills to reduce current and future distress, thus aiding coping and adjustment to the impact of stroke and their role as a carer. The sessions are also intended to increase awareness of the role of thoughts, emotions and behaviours and their influence on each other. By practising problem-solving and stress-management strategies, it is hoped that carers will experience fewer difficulties with their mood in the future.For each session, there will be a presentation containing information about a topic and exercises to aid discussion. Sessions will be presented on Microsoft PowerPoint, and all participants will receive either electronic or paper copies of the slides as appropriate, accompanied by the exercise and an in-between session task. The topics will cover, for example, an introduction to stroke and caring, adjustment and mood, how to handle negative emotions and thoughts, dealing with problems and a well-being relapse prevention plan (which provides a set of coping mechanisms to deal with individual triggers of the stress response in relation to the role as stroke carers to encourage and foster positive mental health). The content of these sessions was informed by the findings of earlier work described above. Relaxation exercises at the end of each session will allow participants to feel calm and relaxed before finishing their session and will also be an effective tool for them to use outside of the session when experiencing high levels of anxiety or distress. Between session tasks will be set to encourage participants to practice exercises from the sessions in their own time. Participants who are identified to be experiencing significant issues that are out of the scope of the intervention will be referred onto the appropriate specialist service, subject to their consent.

### Outcomes

The main outcome for the study is to determine the feasibility of conducting a larger, powered study. This will be a composite of: whether the eligibility criteria are realistic; whether stroke survivors and carers are willing to be randomised; the study attrition rate; the feasibility and acceptability of delivering the intervention; the suitability and sensitivity of outcome measures; and the most suitable outcome measure for use in the main study.

The stroke carer outcomes to be assessed at 6 months postrandomisation will be: anxiety and depression, health-related quality of life and carer strain. The outcome measures that will be used are: Hospital Anxiety and Depression Scale,^35^ EuroQol 5D-5L^36^ and the Caregiver Burden Scale.^37^

The stroke survivor outcomes to be assessed 6 months postrandomisation will be: level of disability, ability to perform personal activities of daily living, level of anxiety and depression and health-related quality of life. The outcome measures that will be used are: Modified Rankin Scale,^38^ Barthel Index,^39^ Hospital Anxiety and Depression Scale^35^ and EuroQol 5D-5L.^36^ The timeline and proposed flow of participants through the study is shown in figure 1.

**Figure 1 F1:**
[figure not shown]
Flow of participants through the study.

### Feedback interviews

Qualitative semistructured interviews will be conducted with carers in both arms of the trial, within 2 weeks of their final outcome assessment. Up to 10 interviews will be completed with stroke carers in each arm. Our aim is to obtain feedback on all aspects of the study in addition to the intervention procedures, assessments, intervention (if received) and perceived outcomes. For those in the control group, the interviews will provide confirmation of the nature of usual care received. Participants will be purposefully selected to include carers of stroke survivors with varying severity of stroke, age and gender. The interviews will be conducted by a researcher who had no involvement in the intervention delivery, thereby reducing social desirability response bias. The researcher conducting the interviews will become aware of the group allocation during the interview and so will not be masked to the intervention. These interviews will be audio recorded using a digital recorder, transcribed and analysed using a thematic analysis (following the procedure described by Braun and Clarke^40^). The interviews with participants will provide information feedback on their perception of progress over time and for those in the intervention group, the quality of the intervention provided, and as such will serve as a process measure. Insights from the qualitative data and analysis will serve to inform developments of the intervention programme in the future and to generate user-orientated proposals about areas for further investigations. This information will also inform us of any refinements to be made to the study procedures. An interview will also be conducted with the group facilitator after they have completed all therapy. This interview will ask about the ease of delivery of the intervention according to the manual and any challenges.

### Sample size, recruitment strategy, randomisation and blinding

For a feasibility study, no formal sample size calculation is required. The aim is to recruit up to 40 dyads (20 in each arm of the trial) to test the randomisation process and the feasibility of the study processes of delivering the intervention. This target should allow us to collect sufficient information on the suitability and sensitivity of the outcome measures for use with this population and the SD of the measures to inform a sample size calculation for a definitive trial. The median sample size for UK feasibility trials has been reported at 36,^41^ which is broadly consistent with the planned target.

The trial opened for recruitment on 1 November 2015 and will close on 31 July 2017 or when 40 dyads have been recruited (whichever is soonest). Participants will be enrolled into the study by a member of staff from the Clinical Research Network or a member of the research team. The process for obtaining participant informed consent will be in accordance with the Research Ethics Committee guidance, Good Clinical Practice and any other regulatory requirements that might be introduced. Following a full explanation of the study, the participant will be required to provide informed written consent before they can participate. Where a consultee is required for a stroke survivor, the consultee shall provide a recommendation as to whether they consider the person would have agreed to take part in the study had they still had capacity to state their own preference. They will sign the consultee declaration should they believe that person would have wished to take part in the study.

Participants will be randomised at baseline following consent and completion of the baseline assessments. Randomisation to each group will be on a 1:1 basis—intervention:control. A simple randomisation procedure will be provided and overseen by the East Midlands Research Design Service. The group facilitator will be informed of group allocation as they will be providing the treatment. We will take every step to minimise allocation and outcome bias.

Trial participants will not be masked to group allocation because they will need to be informed as to whether they have been allocated to the intervention group receiving the biopsychosocial intervention or the control group. The participants’ names, trial identifier numbers and treatment allocation will be stored on a password-protected database held by the group facilitator. This database will be used to allow treatment allocations to be identified at the end of the study.

Baseline data will be collected, and baseline assessments will be completed prior to randomisation. Baseline information will include:demographic details including age, gender, ethnicity and employmentlevels of anxiety and depression (Hospital Anxiety and Depression Scale)quality of Life (EuroQol)carer strain (Carer Burden Scale).

In addition, we will collect the following information from the stroke survivor and/or their medical notes (with consent):stroke characteristicslanguage and cognitive abilities (Montreal Cognitive Assessment)personal activities of daily living (Barthel Index)stroke severity (National Institute of Health Stroke Scale)quality of life (EuroQol)which service (if any) the stroke survivor is discharged to (eg, Early Supported Discharge and intermediate care).

Follow-up assessment visits will be completed at 6 months postrandomisation by a research assistant who is masked to allocation. To minimise the risk of unmasking, prior to each contact, the participant will be reminded that the researcher who is to conduct their follow-up assessment is masked. It is possible that participants may reveal their group allocation to the outcome assessors and any instances of this will be recorded by researchers as part of the assessment of feasibility; researchers will also be asked to make their ‘best guess’ as to the group allocation of the participants to determine whether masking was successful. Other members of the research team and investigators will not be masked to group allocation for the purpose of managing the trial and delivering the interventions. It will not be possible to mask participants.

### Data collection, management and analysis

Data will be collected on a paper case report form (CRF) and will subsequently be entered onto a secure, password-protected, purposely designed electronic database. Each participant will be assigned a trial identity code number, allocated at randomisation, for use on CRFs, other trial documents and the electronic database to ensure confidentiality. The documents and database will also use their initials and date of birth. CRFs will be treated as confidential documents and held securely in accordance with regulations.

When data collection is complete, a data quality check will be conducted in duplicate by two researchers, and a 10% sample of the database will be checked against the original paper CRF. Steps will be taken to minimise missing data by personal contact throughout the study period from the investigator, and every attempt will be made to locate participants for follow-up. Where participants are unavailable for follow-up, details of the attempts to contact them will be recorded. Outcome data will be collected in person, in the participant’s home, by a research assistant to minimise the amount of missing data. For each outcome measure used where data are missing, an imputed average will be used for items where less than 10% of the overall measure is missing. Where more than 10% of a measure is missing, the entire measure will be coded as missing, unless the scoring criterion for that measure stipulates an alternative approach. We will not collect any further data for participants who withdraw from the study, but we will retain all data collected up until the point of withdrawal.

The following procedures will apply to data analysis.

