#### Outcome measures

Outcome measure data will be stored in a database, and data will be analysed using the statistical package STATA (version 13). The proportion of missing items will be examined. The questionnaire data will be analysed to determine the distributions of scores. The analysis will use descriptive statistics and CIs for the parameters we are estimating. The characteristics of stroke survivors and their carers will also be described using means, SD and ranges for quantitative variables and counts and proportions for categorical variables. Data will be analysed on an ‘intent to treat’ basis. Any changes in the planned statistical methods will be documented in the report.

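### The default missing-item rule works on the whole instrument, so it can discard a fully answered anxiety or depression score because of gaps in the other one

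*Protocol article*

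**What the plan says.** The rule is in the Protocol article under Data collection, management and analysis. For each outcome measure, "an imputed average will be used for items where less than 10% of the overall measure is missing". The next sentence deals with larger gaps: "Where more than 10% of a measure is missing, the entire measure will be coded as missing". That second sentence carries an exception, which applies the deletion "unless the scoring criterion for that measure stipulates an alternative approach". Both sentences take the whole instrument as the unit. Subscales are not mentioned, and the article does not say whose average is imputed.

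Under Outcomes, "The stroke carer outcomes to be assessed at 6 months postrandomisation will be: anxiety and depression, health-related quality of life and carer strain". Anxiety and depression are measured with one instrument, the HADS. The stroke survivor outcomes ("level of disability, ability to perform personal activities of daily living, level of anxiety and depression and health-related quality of life") use the HADS as well, so the rule reaches both members of the dyad.

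Under Sample size, recruitment strategy, randomisation and blinding, the target is at most 40 dyads, 20 per arm. The data are meant to show whether the measures are suitable and to supply SDs for the sample size of a definitive trial. Under Outcome measures, "The proportion of missing items will be examined".

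**The concern.** A rule for missing items should act on the score that will be analysed. Here it acts on the questionnaire. When one questionnaire yields two scores, unanswered items belonging to one score count against the other, and a score with every item answered can be coded missing.

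What is at stake is observed data on carer anxiety or depression. These scores feed the SDs for the next trial and the choice of its main outcome. In a sample of at most 40 carers, it is wasteful to discard complete scores for a reason unrelated to their own completeness.

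There is also a small drafting gap. The two sentences cover less than 10% and more than 10%, and neither covers exactly 10%.

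**Working it through.** The plan states no figure that can be reproduced, so the check is to apply its rule to countable cases.

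**Inputs from the Protocol article**
- Impute if the share of items missing is below 10% of the measure; code the entire measure missing if it is above 10%; a measure's own scoring criterion can override the second part.
- At most 40 carers, 20 per arm.

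**Assumptions, because the article gives no item counts or scoring criteria**
- HADS: 14 items, 7 for anxiety and 7 for depression, scored separately.
- No overriding scoring criterion for the HADS.

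**Step 1: the whole-instrument rule on 7 + 7 items**
- One item missing: 1/14 = 7.1%, below 10%, so it is imputed.
- Two items missing: 2/14 = 14.3%, above 10%, so both scores are coded missing.

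**Step 2: where the two missing items fall**

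Suppose exactly two of the 14 items are missing, at random.
- Both in the same subscale: 2 × C(7,2) / C(14,2) = 2 × 21 / 91 = 42/91 = 46%. The other subscale is complete and is lost.
- One in each subscale: 7 × 7 / 91 = 49/91 = 54%. Each subscale has six of seven items answered, and both are lost.

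These shares are conditional on exactly two missing items. They say nothing about how often that happens.

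**Step 3: sensitivity to the assumed layout**

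For two equal subscales of 3 to 15 items each, the number of items that must be missing to void the whole instrument runs from 1 (6 or 8 items in total) to 4 (30 items in total, 4/30 = 13.3%). In every layout that number can fall within one subscale while the other is complete. The problem therefore does not depend on the 7 + 7 assumption.

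**Step 4: the 10% limit moved to subscales unchanged**
- One of seven missing: 1/7 = 14.3%, above 10%, so that subscale would be deleted. The present rule imputes it (step 1).
- The same holds for any subscale of nine or fewer items, since 1/9 = 11.1%.

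The unit and the limit must therefore change together.

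**Step 5: the boundary at exactly 10%**

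With m of k items missing, m/k = 1/10 requires k to be a multiple of 10. Up to 40 items this means 1 of 10, 2 of 20, 3 of 30 and 4 of 40. It cannot occur with 14 items. On an assumed 10-item measure, one missing item is exactly 10% and has no rule, while two missing items are 20% and void the measure.

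**Step 6: size of a loss**

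One lost score is 1/40 = 2.5% of the full sample, or 1/20 = 5% of one arm.

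**The case against.** The strongest reply is the exception. The deletion sentence gives way to a measure's own scoring criterion, and that is where subscale handling would normally sit. If the HADS scoring criterion treats its subscales separately, the loss in step 2 does not occur. This stands: the article does not reproduce any scoring criterion, so the concern holds only where none overrides the default. A reader might infer that complete scores will be lost; the article supports only that they can be.

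Second, outcome data are collected in person, at home, by a research assistant, with the stated purpose of limiting missing data. Two or more blank items in one questionnaire may be uncommon. This also stands, and the 46% must not be read as an expected rate.

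Third, a reader might infer that the rule inflates the missingness reported as a feasibility result. The article does not support that. Missing items are to be examined in their own right under Outcome measures, and Integrity of the study protocol lists missing data and completion of each measure separately. An item-level report is not altered by how scores are later coded.

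Fourth, a reader might take the gap at exactly 10% to leave the most usual case without a rule. The article gives no data on how items go missing. The gap needs an item count that is a multiple of 10, and it does not touch the HADS at 14 items.

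What remains is that the stated default uses the wrong unit for an instrument that yields two scores.

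**Conclusion.** The point holds as a minor, conditional weakness in a rule that the protocol itself fixes. By default, gaps in one HADS subscale can delete a fully answered other subscale. With 7 + 7 items this happens once two items of the same subscale are missing (14.3% of the instrument). It rests on three assumptions: the item counts, separate scoring of anxiety and depression, and no overriding scoring criterion. Step 3 shows that the first is not critical; the third is.

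The likely effect is the loss of a few records at most from the descriptive summaries and SDs, each 2.5% of 40 carers. The planned analysis is descriptive with confidence intervals, so no test result depends on it. The change is worth making because it costs almost nothing and keeps data already collected.

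**What to change.** Replace the two sentences with a rule per score, for example:

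*Missing items are handled separately for each scored subscale, or for the total where an instrument gives a single score. If 10% or fewer of its items are missing, they are replaced by that person's mean of the answered items; otherwise that score is coded missing. For each 7-item HADS subscale, one missing item is allowed and is replaced by that person's mean of the other six. An instrument's own scoring criterion takes precedence over all of these rules.*

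On the assumed layout, with two missing items in one subscale, that subscale is coded missing (2/7 = 28.6%) and the complete one is kept. With one missing in each, both are kept. The one-item allowance should be tied to named subscales, so that it does not start imputation in short single-score measures that the present rule codes as missing.

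The words for 10% or fewer also settle the boundary; assigning exactly 10% to the other side would serve equally well, provided that it is assigned.

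The cost is one or two sentences of wording. The downside is slight measurement error in a subscale score with one imputed item.

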#### Acceptability of the study design

Descriptive statistics will be presented for the following feasibility outcomes: recruitment rates, proportion of carers screened who are eligible for enrolment and who provided consent, how easily carers can be identified, who met the criteria for the study, number of people who accepted intervention to take part in the RCT and number of individuals who attended the intervention/number of sessions they attended. The feedback interviews will provide further information regarding the acceptability of the intervention. Qualitative thematic analysis will provide an insight into carer perspectives of their experience of caring and what effect they think the intervention itself may have had (for the treatment group).

